## Abstract

**Background:**

Treatment of pulmonary sarcoidosis is recommended in case of significant symptoms, impaired or deteriorating lung function. Evidence-based treatment recommendations are limited and largely based on expert opinion. Prednisone is currently the first-choice therapy and leads to short-term improvement of lung function. Unfortunately, prednisone often has side-effects and may be associated with impaired quality of life. Methotrexate is presently considered second-line therapy, and appears to have fewer side-effects.

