**Methods/design:**

In this prospective, randomized, non-blinded, multi-center, non-inferiority trial, we plan to randomize 138 treatment-naïve patients with pulmonary sarcoidosis who are about to start treatment. Patients will be randomized in a 1:1 ratio to receive either prednisone or methotrexate in a predefined schedule for 24 weeks, after which they will be followed up in regular care for up to 2 years. Regular hospital visits will include pulmonary function assessment, completion of patient-reported outcomes, and blood withdrawal. Additionally, patients will be asked to perform weekly home spirometry, and record symptoms and side-effects via a home monitoring application for 24 weeks.

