- Difference in change in FVC % predicted at 4, 16 weeks, 1 year and 2 years between prednisone and methotrexate group - Time to major pulmonary improvement measured by home-measured FVC, whereby major pulmonary improvement is defined as 80% of the maximum percent predicted FVC reached anywhere during the first 24 weeks of treatment - The percentage of patients with ≥5 and ≥ 10% improvement or decline in FVC at 4, 16 and 24 weeks - The percentage of patients with ≥10% improvement or decline in DLCO at 4, 16 and 24 weeks - Change over time in (Health-related) quality of life measured by King’s Sarcoidosis Questionnaire (KSQ), Global Rating of Change scale (GRoC), Chronic Respiratory Questionnaire (CRQ) and Euroqol-5D-5L questionnaire (EQ-5D-5L) at every clinical visit - Time to symptom improvement. Symptom scores measured by Visual Analogue Scales (VAS), Medical Research Council dyspnea scale (MRC) and Fatigue Assessment Scale (FAS) - Expectations with medication at baseline - Experiences and satisfaction with medication measured by the Patient Experience and Satisfaction with Medication Questionnaire (PESaM) - Number, severity and impact of side-effects compared between methotrexate and prednisone - Number of patients who discontinue/switch medication - Adherence to treatment schedule (% of patients that received at least 90% of the total cumulative dose after 24 weeks). - Correlation between angiotensin coverting enzyme (ACE), serum soluble interleukin-2 receptor (sIL-2R) and clinical parameters	
Explorative endpoints	
- Asses predictors of disease progression and response to therapy - Correlations between biomarker characteristics and clinical parameters - Change in biomarkers over time - Explore potential differences in distribution/phenotypes of monocytes, Th-cells, dendritic cells and new biomarkers identified using proteomics between patients during treatment with prednisone or methotrexate at all points	

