- Diagnosis of sarcoidosis according to the ATS/ERS/WASOG criteria [6], in case of absent histology a diagnosis of sarcoidosis can also be established in a multidisciplinary team meeting in a sarcoidosis expert center based on a highly suggestive clinical and radiological picture [22] - Age ≥ 18 years - A pulmonary indication for treatment and parenchymal involvement on X-ray or chest CT-scan conducted within three months before inclusion (determined by the treating physician and according to current guidelines) - A forced vital capacity (FVC) of ≤90% of predicted, or a diffusion capacity of the lung for carbon monoxide (DLCO) ≤70% of predicted, or an absolute decline of ≥5% FVC decline, or an absolute ≥10% DLCO decline in the past year	- Any condition or circumstance that, in the opinion of the investigator, may make a subject unlikely or unable to complete the study or comply with study procedures - Previous immunosuppressive treatment for sarcoidosis - Use of systemic immunosuppressive therapy within the preceding three months for another disease than sarcoidosis - Pregnant, breastfeeding, or planning to become pregnant or breastfeed during the study treatment or within 90 days after the last dose in the randomized study phase. For males; planning to pro-create during the study or within 90 days after the last dose of the randomized study phase - Primary systemic treatment indication being an extra pulmonary location of sarcoidosis (e.g. cardiac of neurological) - Contra-indication for methotrexate or corticosteroids^a^

^a^Contra-indications for methotrexate or corticosteroids are defined as: severely impaired renal function (creatinine clearance < 30 ml/min), impaired hepatic function (serum bilirubin-value > 5 mg/dl or 85,5 μmol/l), bone marrow insufficiency with severe leukopenia, thrombocytopenia, or anaemia, severe acute or chronic infections, such as tuberculosis, human immunodeficiency virus, parasitic infections or other immunodeficiency syndromes, mouth, stomach or duodenal ulcers

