### Home monitoring

For home monitoring of pulmonary function, symptoms and side-effects, a home monitoring application will be used, which has previously been developed together with sarcoidosis patients [21]. The application will be installed on a smartphone or tablet. In this CE-marked, secured application (Curavista, the Netherlands), patients will keep track of their own data, such as pulmonary function, side-effects and symptoms. A graphic overview of results is available, so patients can gain more insight in their disease course, an example is shown in Fig. 2. A handheld spirometer (Spirobank Smart, MIR, Italy) will be handed out to all patients. Patients will be instructed to undertake spirometry (three consecutive measurements) once a week at the same day, at approximately the same time to enhance compliance and reduce variability [23]. The best result of the day will be transmitted real-time to the patients’ personal platform and will be directly accessible for both patients and the study team. This will enable close monitoring and early detection of possible deterioration. On the same day as spirometry, patients will report their symptoms and, if any, side-effects on their personal platform. Patients record cough, dyspnea, fatigue, and general complaints on a visual analog scale (VAS) and will also report dyspnea on the Medical Research Council scale (MRC). In case of side-effects, patients can record which side-effects they have and how bothersome they are. When FVC declines ≥10%, or side-effects are burdensome, an email alert will be sent directly to the treating physician, who will contact the patient within 24 h to discuss symptoms and decide whether an extra outpatient clinic visit with pulmonary function measurement is needed. Furthermore, patients will be asked to complete PROMs at every time point before the doctor’s visit.

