### Statistical analyses

The primary analysis will be based on the Intention-to-Treat (ITT) population, defined as all randomized patients who received at least one dose of prednisone or methotrexate. Patients who discontinue treatment prematurely will be analyzed based on the available data. As a sensitivity analysis, a Per Protocol analysis will be performed in all enrolled patients who complete the 24 week treatment regimen without major protocol violations. Change in FVC (% predicted) between baseline and 24 weeks follow-up will be compared between the two groups by using multilevel analysis with the repeated values of FVC as dependent variable and groups, time (defined as categorical variable) and baseline FVC as covariate. To account for the repeated FVC measurements, patient will be included as a random effect. Additionally the interaction terms between the time points and group will be added to assess at which point in time the groups have different average FVC values.

(Generalized) multilevel analyses will also be used to evaluate within and between-group differences in pulmonary function, symptoms, QoL scores, and side-effects over the study period. Between-group differences in mean time to onset of side-effects and time to symptom improvement will be analyzed using Kaplan Meier and log rank test. The Chi square test will be used to evaluate between-group differences in the proportions of patients who discontinue medication, proportion of patients who have FVC improvement and FVC decline, and the proportion of patients who adhere to the treatment schedule. The time to pulmonary improvement, using home spirometry, will be assessed using a linear mixed model, with FVC as dependent variable and time and treatment group as independent variables. Time will be entered as a random effect and will be modelled flexible. Moreover, this model will incorporate the change in curvature of the FVCs temporal trajectory, and thus enable estimation of the time point at which the maximum improvement in lung function is reached. Correlation between lung function, side-effects, QoL scores and symptoms will be analyzed with Pearson Correlation Coefficient. The FVC trajectory over time will be related to the trajectory of QoL scores over time with a linear mixed model. Logistic regression will be used to analyze which clinical or laboratory parameters are associated with disease progression (defined as ≥10% FVC decline) and disease chronicity.

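### The log-rank test for time to symptom improvement ignores the baseline symptom score and can lose a material part of its power; stratifying by or adjusting for that score costs almost nothing

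*Protocol article*

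**What the plan says.** The endpoint is secondary. Table 1 of the protocol article (Objectives and endpoints) lists it as "Time to symptom improvement. Symptom scores measured by Visual Analogue Scales (VAS), Medical Research Council dyspnea scale (MRC) and Fatigue Assessment Scale (FAS"). It prints no improvement threshold. Under Home monitoring, "Patients record cough, dyspnea, fatigue, and general complaints on a visual analog scale (VAS") and also grade dyspnea on the MRC scale; the abstract says they will "record symptoms and side-effects via a home monitoring application for 24 weeks". The FAS is collected at hospital visits. Counting the four VAS items, MRC and FAS gives six scales.

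Under Statistical analyses the test is fixed: "time to symptom improvement will be analyzed using Kaplan Meier and log rank test". No stratification factor or covariate is named. In the same section the primary FVC model does include the baseline value as a covariate.

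Eligibility (Table 2) rests on a pulmonary indication, parenchymal involvement and any one lung-function criterion, beginning with "A forced vital capacity (FVC) of ≤90% of predicted, or a diffusion capacity of the lung for carbon monoxide (DLCO) ≤70% of predicted" and continuing with recent decline in either measure. No symptom score is required. The abstract's Background gives the same alternatives: "Treatment of pulmonary sarcoidosis is recommended in case of significant symptoms, impaired or deteriorating lung function".

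Two further statements bear on the point. The analysis set is named for the primary endpoint: "The primary analysis will be based on the Intention-to-Treat (ITT) population". Symptoms are also compared by repeated-measures models: ("Generalized) multilevel analyses will also be used to evaluate within and between-group differences in pulmonary function, symptoms, QoL scores, and side-effects" over the study period).

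**The concern.** Improvement is a change from the patient's own starting score. Someone with no cough at baseline cannot improve on cough, and someone with a low score may need nearly complete relief to reach an absolute threshold. The baseline score is therefore likely to be the strongest known determinant of the event time, and the stated test does not use it.

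Two losses follow. First, any patients at the floor who are in the risk set stay there as not improved. As the faster arm uses up the patients who can improve, its risk set fills with those who cannot. Late events then come mainly from the slower arm and offset the early difference. Second, even with nobody at the floor, differences in starting score spread the event times and blur the contrast.

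The article's Discussion presents early response to therapy as something the home monitoring should evaluate better. A null result from a weak test could be read as equal speed of relief. If floor patients are included, the Kaplan-Meier plateau also mixes failure to respond with absence of the symptom.

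**Working it through.** **1. The plan's own figure.** The sample size concerns FVC only: margin 5, SD 10.5, one-sided 5%, power 80%.

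n per arm = 2 × (1.645 + 0.842)² × 10.5² / 5² = 2 × 6.18 × 4.41 = 54.5, so 55 per arm and 110 in total. With 20% dropout, 110 / 0.8 = 137.5, so 138, or 69 per arm. Both stated figures reproduce. No power is stated for time to symptom improvement.

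**2. The mechanism, by hand (assumed inputs).** Let a share f = 0.30 be unable to improve. Let the others improve at h = 0.10 per week in the slower arm and 0.18 in the faster arm (hazard ratio 1.8). If all stay in the risk set, the observed hazard at week t is h × 0.7e^(−ht) / (0.7e^(−ht) + 0.3).

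| Week | Slower arm | Faster arm | Ratio |
|---|---|---|---|
| 0 | 0.0700 | 0.1260 | 1.80 |
| 12 | 0.0413 | 0.0382 | 0.92 |
| 24 | 0.0175 | 0.0054 | 0.31 |

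The ratio starts at 1.8 and is below 1 by week 12. With 55 per arm this setting gives power of 20% with everyone kept and 69% in those able to improve. It is close to a worst case, because 1 − e^(−2.4) = 91% of improvable slower-arm patients improve by week 24.

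**3. Keeping against excluding floor patients.** Assumed: 138 patients, 1:1, weekly scores to week 24, about 20% dropout, two-sided 5% log-rank, 1,000 runs, hazard ratio 1.75. Each cell gives power kept v excluded.

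| Share at floor | 50% of the rest improve | 70% improve | 90% improve |
|---|---|---|---|
| 10% | 0.58 v 0.63 | 0.61 v 0.74 | 0.58 v 0.82 |
| 20% | 0.49 v 0.60 | 0.48 v 0.70 | 0.39 v 0.81 |
| 30% | 0.39 v 0.52 | 0.37 v 0.65 | 0.23 v 0.71 |
| 50% | 0.25 v 0.39 | 0.25 v 0.54 | 0.13 v 0.57 |

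(The percentage improving is for slower-arm patients with room to improve, by week 24.) The same grid at hazard ratio 2.0 makes 24 scenarios. The relative loss, 1 − kept/excluded, ran from about 6% (1 − 0.774/0.824) to 78% (1 − 0.162/0.751). It exceeded one half in 7 of 24: four with 50% at the floor and 70% or 90% improving, two with 30% at the floor and 90% improving, and one with 20% at the floor and 90% improving. At 10% at the floor it was about 6-29%. Simulated type I error with these patients kept was 0.04-0.05.

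**4. Using the baseline score.** Assumed: 69 per arm, 20% dropout, 10-20% non-responders, improvement of 2 VAS points. Same patients in both columns, nobody excluded.

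| Share at floor | Plain log-rank | Stratified by baseline |
|---|---|---|
| 0% | 36% | 45% |
| 15% | 17% | 32% |
| 30% | 9% | 31% |

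Type I error was about 5%. With a relative threshold (30% fall) stratification brought no gain.

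A more favourable setting (55 per arm, time constants 5 v 8 weeks, noise SD 0.5, every patient with room responding) gave, for everyone plain / restricted plain / restricted and stratified by thirds: 77/78/99% with none at the floor, 32/72/97% at 15% and 15/64/94% at 30%. The stratified gain there is flattered by low noise. At 30% at the floor, noise SD 1.0 gave 8/31/46%, and 20% non-responders with noise SD 0.5 gave 10/20/34%.

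**The case against.** The strongest objection is that the article condenses a fuller document. Event definition and risk set for a secondary endpoint normally stand in the full protocol or SAP, which are not shown. This is right as far as the risk set goes. A reader might infer that the test covers all patients, including those without the symptom at baseline. The article does not say so: it names the ITT population for the primary analysis only and is silent on the set for this endpoint.

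A reader might also infer that the test loses most of its power. That too is unsupported. It needs a floor share, a response rate and a hazard ratio that the article does not give, and it failed in 17 of the 24 scenarios above.

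The unadjusted log-rank test is valid under randomisation, so it is not an error in itself. The endpoint is secondary and unpowered. The multilevel models of symptoms offer another between-group comparison that does not depend on a yes/no event, although they do not estimate time to improvement.

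What remains is narrower. The article names a method, and that method omits a baseline value that is already collected and strongly related to the outcome, while the primary analysis in the same section uses its own baseline value. That is a choice which can be improved, not only a missing detail.

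**Conclusion.** The point holds in a limited form. The planned test is valid, but it leaves out the baseline symptom score and can thereby lose a material part of its power. With an absolute 2-point threshold the assumed scenarios put the cost of not stratifying, in the same patients, at 9 percentage points with nobody at the floor (45 − 36), 15 with 15% there (32 − 17) and 22 with 30% there (31 − 9). With a relative threshold it may be negligible.

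All these sizes rest on assumed floor shares, response rates, noise and thresholds; the article fixes none of them. Whether floor patients would be in the risk set at all is also unknown. The primary FVC comparison is not affected.

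**What to change.** For each symptom scale, replace the plain log-rank test by one stratified by baseline score (for example thirds), or by a Cox model with baseline score as covariate. Unless the SAP already does so, limit each analysis to patients whose pre-treatment score leaves room for the defined improvement, and report per arm how many were excluded. The restriction uses a pre-treatment value, so the randomised comparison is kept.

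The cost is a change of wording, with no new data. The downside is fewer patients per scale, a population that differs from scale to scale, and a conclusion that applies to patients who have the symptom. The restriction also requires the improvement threshold to be stated for each scale.

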### Serum and cellular biomarkers

Blood samples will be analyzed in order to study both serum and cellular biomarkers. With regards to serum biomarkers, the value of existing biomarkers such as ACE and sIL-2R in predicting disease progression or response to therapy will be studied prospectively. Furthermore, a proteomics approach will be used to search for possible new biomarkers in sarcoidosis. Regarding cellular biomarkers, the amount of Th17-lineage cells, DCs and monocytes will be analyzed in order to predict response for individual patients to prednisone and/or methotrexate.

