### Sample size calculation

The power calculation is based on data from a previous observational study with prednisone in newly treated patients with pulmonary sarcoidosis. In this study, the mean increase in FVC with prednisone was 15%, with a standard deviation of 10.5% [8]. In a case series of 50 patients with sarcoidosis treated with methotrexate, treatment effect was in line with the findings for prednisone; 66% of patients had more than 15% improvement in vital capacity after 6 months [24]. We chose a non-inferiority margin of 5%, because FVC measurements show biological variation and thus variation < 5% is not considered clinically relevant. Based on these numbers, using a one-sided test with a power of 80% (β) and a type 1 error of 5% (α), the estimated sample size of this study is 110 patients. To allow for 20% drop-out, we aim to randomize 138 patients.

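### On the plan's own inputs about 1 of 110 patients would show a ≥10% FVC decline by week 24: too few for the stated Chi square comparison, and for the progression model if it is read within that period

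*Protocol article*

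**What the plan says.** The Statistical analyses section of the protocol article plans logistic regression for clinical or laboratory parameters "associated with disease progression (defined as ≥10% FVC decline) and disease chronicity". It states neither the period over which the decline is counted nor the value it is measured from. The same section names the Chi square test for the "proportion of patients who have FVC improvement and FVC decline". Table 1 makes these proportions a secondary endpoint, with thresholds of 5% and 10% at weeks 4, 16 and 24. Predictors of progression and of response appear there as explorative endpoints.

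The Sample size calculation section takes its input from an earlier observational study of prednisone, in which "the mean increase in FVC with prednisone was 15%, with a standard deviation of 10.5" per cent. For methotrexate it cites a case series in which the "treatment effect was in line with the findings for prednisone". No expected number of patients with a decline is given anywhere in the article.

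**The concern.** The article sizes the trial on a large average gain in both arms, then fixes two analyses whose outcome is a substantial loss. If nearly everyone improves, almost nobody supplies an event. A Chi square test on almost empty cells does not hold its nominal error rate. A logistic model with one or two events separates, fails to converge or returns very large odds ratios by chance.

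At stake are one part of a secondary endpoint and one of the explorative aims. Both methods and the 10% threshold are stated in the article, so the objection is to what is written, not to detail left to an analysis plan.

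**Working it through.** **Inputs.** From the Sample size calculation section: mean gain 15, SD 10.5, methotrexate similar to prednisone, margin 5, one-sided 5% error, 80% power, 110 evaluable patients, 20% drop-out, 138 randomized. From Design and participants: 1:1 allocation. My assumptions: FVC change is normally distributed, with gain and decline expressed on the same scale.

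**The plan's own figure first.** For non-inferiority of means with no true difference, n per arm = 2 × (1.645 + 0.842)² × 10.5² / 5² = 54.5, rounded up to 55, so 110 in total. Allowing for drop-out, 110 / 0.8 = 137.5, so 138. Both stated figures reproduce.

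**Expected declines at one on-treatment visit.**

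- Decline ≥10%: Φ((−10 − 15)/10.5) = Φ(−2.38) = 0.0086. This gives 110 × 0.0086 = 0.95 patients, or 1.19 of 138. The chance of no such patient at all is (1 − 0.0086)^110 = 39%, or 30% with 138.
- Decline ≥5%: Φ((−5 − 15)/10.5) = 0.0284. This gives 3.1 of 110, or 3.9 of 138.

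Per arm this is about 0.5 patients for the 10% threshold (0.95 / 2) and about 1.6 for the 5% threshold (3.1 / 2). The usual guide for the Chi square approximation is an expected count of at least 5 per cell.

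**Variants for the ≥10% decline (all assumptions of mine).** The ranges in the first, third and fourth rows run from 110 to 138 patients; the second also spans the two baselines.

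| Variant | Expected patients in total |
|---|---|
| Methotrexate mean lower by the full margin (+10) | 2.0 to 2.6 |
| Decline taken as 10% of a baseline of 90 or 70% predicted (9 or 7 points) | 1.2 to 2.5 |
| Heavier tails, t with 3 or 5 degrees of freedom, same SD | 1.4 to 1.9 |
| Decline at any of three visits, treated as independent: N × (1 − (1 − 0.0086)³) | 2.8 to 3.5 |

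So the inputs imply about 1 to 4 patients in total by week 24, or about 0.5 to 2 per arm.

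**What would supply enough events.** About 10 in total would need a mean gain of only about +5 at SD 10.5 (Φ(−15/10.5) = 0.077, giving 8.4 to 10.6), or +10 at SD 15 (Φ(−20/15) = 0.091, giving 10.0 to 12.6). Neither is the planning assumption.

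**The case against.** The strongest reply concerns time. The 15% gain describes response to newly started treatment, whereas the article does not tie progression to 24 weeks. It pairs progression with chronicity, follows FVC at 1 and 2 years, and allows treatment to be reduced after week 24. If the mean change from baseline had faded to 0 by then (an assumption), Φ(−10/10.5) = 0.17, or about 19 of 110. Decline counted from the best value could also be more frequent. This stands: a reader might infer that the progression model cannot work at all, and the documents do not support that. They give no FVC figures for the later period in either direction.

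The inputs may also not transfer. Patients can enter on DLCO criteria alone and may have less room to gain FVC, and the article says that data on time to improvement under methotrexate are lacking, so early visits in that arm could look different. That is fair, and it is why the count is given as a range.

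A reader might also infer that the whole predictor and biomarker programme fails. It does not. The chronicity model, the prediction of response (blood markers "will be analyzed in order to predict response for individual patients to prednisone and/or methotrexate"), the improvement proportions, biomarker change over time and the correlations need no ≥10% decline.

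Nor is the outcome necessarily distorted because the treatment schedule adds the other arm's drug after an absolute decline of ≥10%. If progression means ever reaching that decline, the addition comes after the event. Only a reading at a later fixed visit would be affected, and the article does not say which applies.

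Finally, exact tests and penalisation are often left to an analysis plan. Here, though, the article itself names the Chi square test and the logistic model on this event.

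**Conclusion.** The point holds in a limited form. On the plan's own mean and SD, about 1 of 110 evaluable patients (about 1 to 4 under the variants shown) would have a ≥10% FVC decline by week 24, and about 3 of 110 a ≥5% decline. The Chi square test for the decline proportions is then the wrong tool, and the logistic model for progression lacks events if it is read within 24 weeks. Whether follow-up to 2 years would rescue that model cannot be judged from the article.

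This rests on a roughly normal distribution with similar means in the two arms, and on the prednisone study's figures carrying over to this population. The primary analysis and the 110/138 sample size are untouched. The affected outcomes are part of a secondary endpoint and an explorative analysis, so this is a worthwhile correction and no threat to the trial's main conclusion.

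**What to change.** - Compare the ≥5% and ≥10% decline proportions with an exact test, and report the counts and the risk difference with an exact or score confidence interval. With so few events the interval carries the information.
- Make continuous FVC % predicted the main outcome of the predictor analysis, in a mixed model with a parameter × time term. The article already uses mixed models for FVC, and every patient contributes.
- Keep the binary ≥10% progression model as supportive only. State its window (including 1 and 2 years) and its reference value, use Firth-penalised logistic regression, and limit it to very few predictors.
- Do not replace progression with a gain of less than 10%. That would supply more events (Φ((10 − 15)/10.5) = 0.317, about 35 of 110), but it measures non-response and would count stable patients as progressing.

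The cost is wording only, since all the data are already planned. The one drawback is that the main predictor result is read per FVC point and not as an odds ratio of progression.
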